### Objectives and endpoints

The primary objective of this study is to determine the effectiveness of home-based contact management, including TPT initiation and follow-up, using community-based healthcare workers to increase TPT initiation as compared to facility-based contact management. The primary endpoint is the cluster-level ratio of the number of household child contacts less than 15 years of age in Ethiopia and less than 5 years of age in South Africa initiated on TPT (3HP, 3RH, or 6H) per index patient, comparing the intervention to the control arm (Table 1). Because we anticipate heterogeneity in the epidemiology of TB and potential differences in the response to the intervention between countries, the primary outcome will be assessed across countries and within countries.

**Table 1 Tab1:** Primary and secondary outcomes for the CHIP-TB trial

**Primary outcome**	**Outcome description**	
TPT initiation among child contacts	The cluster-level ratio of the number of household child contacts less than 15 years of age in Ethiopia and less than 5 years of age in South Africa initiated on TPT per index patient, comparing the intervention to the control arm	
**Secondary outcome**	**Outcome description**	
Child contact identification	The cluster-level ratio of the number of household child contacts less than 15 years of age in Ethiopia and less than 5 years of age in South Africa identified per index patient	
Continuum of care	The cluster-level proportions of estimated child contacts who progress through each stage of the pediatric TB prevention continuum of care (identification, screening, initiation, and completion) overall and by age, by TPT regimen, and by country. *estimated child contacts will be calculated using DHS data	
Treatment completion (as defined by WHO TPT Handbook)	• Proportion of children initiated on TPT who successfully completed TPT • Proportion of children initiated on TPT who were lost to follow-up • Proportion of children initiated on TPT with incident TB (treatment failure) • Proportion of children initiated on TPT who died • Proportion of children initiated on TPT who discontinued TPT due to: toxicity, drug-drug interaction, severe illness (e.g., malaria), pregnancy, or family preference *Treatment completion was defined as 11 doses in 16 weeks for 3HP and 68 doses in 4 months for 3RH [19].	
**Implementation outcome**	**Quantitative assessment**	**Qualitative assessment**

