### Study population

The study will attempt to enroll all close child contacts of individuals diagnosed and treated for infectious drug-sensitive TB in the study clinics. Good Clinical Practice (GCP)-trained study and clinic staff will enroll participants. Eligibility criteria for index patients and child contacts are pragmatically designed to align with the Ethiopian and South African National Guidelines regarding TPT eligibility. We will enroll index participants with pulmonary TB disease who (1) are 18 years and older, (2) attend a study clinic for TB care and live in the catchment area of that clinic, (3) are willing to have a home visit and disclose their TB diagnosis to household members, and (4) who provide informed consent. In South Africa, all index patients will need bacteriologic confirmation of pulmonary TB disease by smear, Xpert, and/or liquid mycobacterial culture. In Ethiopia, index patients may have bacteriologic confirmation or clinical diagnosis. Index patients in both countries will be excluded if there is evidence of rifampin and/or isoniazid resistance on Xpert or drug sensitivity testing from isolates identified on culture (late exclusion) or if the household has more than one index patient and whose child contacts have already participated in the study. Child contacts will be enrolled if (1) they are less than 15 years of age in Ethiopia or less than 5 years of age in South Africa, (2) they are a close contact of the index patient, and (3) their parent or legal guardian is willing to provide informed consent. Additionally, in Ethiopia, children 12 years and older must be willing to provide assent. Child contacts in both countries will be excluded if any index patient in their household has drug-resistant TB by either Xpert or drug sensitivity testing. Eligibility criteria will be adapted as country guidelines are updated.

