### Study description and procedures

#### Intervention arm

In the intervention arm, child TB contact management, including contact tracing, child evaluation, and TPT initiation and follow-up, will take place in the community at the child’s home (Fig. 2). Newly diagnosed eligible TB index patients will be asked to give consent to a home visit. The initial home visit will include TB symptom screening for all TPT-eligible children (< 15 years in Ethiopia and < 5 years in South Africa), and either TPT initiation for asymptomatic child contacts or clinic referral for all symptomatic child contacts. TB screening and TPT initiation will be conducted by either a research nurse (South Africa) or health extension worker (Ethiopia) in the home. Children who screen negative (0 of 8 symptoms present, see the “ TB screening and evaluation” section) will be initiated on TPT. Children who screen positive (any one symptom is present) will be counseled and referred to the local clinic for evaluation as per the local standard of care. The community health team (in Ethiopia) or the research nurse (in South Africa) will revisit the household monthly for three months to ensure linkage to care.

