#### TB screening and evaluation

In both the intervention and control arms, eligible children will be clinically evaluated using the national TB screening tool. TB screening will focus on major pediatric symptoms including fever, cough of 2 weeks or more, wheezing, reduced playfulness or unusual fatigue, lethargy, visible mass in the neck, weight loss, or failure to thrive based on clinical report and/or the growth chart in the child’s medical record and immunization record (i.e., Road to Health Booklet). Ultimately the child will either be started on TPT (if TB disease is ruled out) or TB treatment.

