### Data collection

#### Outcome data

Clinical outcome data will be extracted from patient records maintained by the community health teams and the clinic. Outcome variables that will be retrospectively extracted from the child contact file include presence of symptoms (binary, yes/no will be asked for each symptom), gastric aspirate/Xpert/culture results (if applicable), chest X-ray results (if applicable), the TPT or active TB treatment initiation date, the TPT regimen, planned and actual dates of all follow-up visits, TPT completion date, and reasons for early discontinuation including patient preference, pregnancy (adolescents), and severe disease including malaria or side effects including flu-like illness, hypersensitivity reactions, hepatotoxicity, and peripheral neuropathy (if applicable). We will collect information regarding the location of child contact screening, TPT initiation, and all subsequent follow-up visits. We recognize these outcomes are dependent on clinic staff compliance with study tools. Periodic monitoring of study tools will be performed, and additional training will be provided if study tools are not being used optimally.

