### Statistical analysis

#### Primary and secondary outcome analyses

Summary statistics of the enrolled index patients will be presented stratified by arm and study site. Analysis of the primary outcome of the number of child contacts less than of 15 years of age in Ethiopia and less than 5 years of age in South Africa who initiate TPT per index patient diagnosed will be stratified by country. Cluster-level ratios will be compared between arms using an unpaired t-test which has been shown to be robust for a relatively small number of clusters [24]. The ratio of the study arm mean ratios and the corresponding 95% confidence interval will be calculated. A log-transformation of the cluster-level ratios will be applied before applying the *t*-test if the outcomes are highly skewed. If the number of index patients varies substantially between clinics, weighted (by clinic size) mean ratios will be used. If the sample size allows, we will compare the numbers of children started on TPT between arms stratified by TPT regimen (3HP vs 3RH) and children’s age groups (^3^5 vs <5 for Ethiopia).

Secondary outcomes to be compared between arms will be the number of child contacts identified (using index patient’s clinic-based contact tracing report, the child contact management file, and the community-level file maintained by the community health team) per index patient, and the proportions of these who are screened, initiated on TPT and who complete TPT. As done for the primary outcome, cluster-level summaries for secondary outcomes will also be compared between arms. Count outcomes will be compared using Poisson regression, and cluster-level proportions (after a log-transformation, if necessary) will be compared using a *t*-test.

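### In the secondary care-cascade comparison, a child found to have TB and put on TB treatment counts as not initiated and not completed, so those two steps mix treated TB with loss from care

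*Protocol article*

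**What the plan says.** The protocol article, under Primary and secondary outcome analyses, lists as secondary outcomes for comparison between arms the number of child contacts identified per index patient and "the proportions of these who are screened, initiated on TPT and who complete TPT". The denominator there is identified contacts. Cluster-level proportions are compared by t-test, with a log transformation if necessary.

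Table 1, under Objectives and endpoints, has the same steps over a different denominator: "The cluster-level proportions of estimated child contacts who progress through each stage of the pediatric TB prevention continuum of care", where the estimate comes from DHS data.

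TB screening and evaluation describes how evaluation ends: "Ultimately the child will either be started on TPT (if TB disease is ruled out) or TB treatment". In the intervention arm, "Children who screen positive (any one symptom is present) will be counseled and referred to the local clinic for evaluation".

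Under Study population, the disease-related exclusion for children concerns the household's index patients: "Child contacts in both countries will be excluded if any index patient in their household has drug-resistant TB". TB disease in the child is not an exclusion.

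Under Outcome data, the variables to be extracted include "the TPT or active TB treatment initiation date". The only TB-disease outcome in Table 1 is incident TB among children who have already started TPT.

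**The concern.** The cascade has one exit from screening, TPT, while the care pathway has two. A child who is screened, diagnosed and treated for TB has been managed as the article describes, yet is counted as not initiated and, later, as not completed. A symptomatic child who is referred and never reaches the clinic gets the same values at those steps.

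The initiation and completion steps are compared between arms. The two arms also select children into screening differently. Home visits are meant to screen every age-eligible child in the household. Control clinics see the children whom index patients bring, and some referred from the MCH clinic. The share of screened children who have TB may therefore differ by arm, and that difference would be read as a difference in TPT uptake. The gap between screening and initiation would also look larger than the true loss from care in both arms.

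**Working it through.** The article states no figure for this step, so there is nothing to reproduce. The check is the algebra of the definition, followed by assumed values.

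**Definitions**
- s = share of identified contacts who are screened
- t = share of screened children found to have TB (the yield)
- u = share of TB-free screened children who start TPT

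The article gives none of these for its arms. I assume s = u = 0.9 and t from 0% to 10%, and that every child with TB starts TB treatment.

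**Step 1. The measure as written.** Initiated/identified = s × (1 − t) × u = 0.81 × (1 − t).

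| Assumed yield t | Initiated/identified |
|---|---|
| 0% | 81.0% |
| 2% | 79.4% |
| 5% | 77.0% |
| 10% | 72.9% |

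The proportion falls although screening and uptake among TB-free children do not change.

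**Step 2. Two clinics with the same score.**
- Clinic A: 100 identified, 100 screened, 10 on TB treatment, 90 on TPT. Initiation is 90%.
- Clinic B: 100 identified, 90 screened, 10 never reached, 90 on TPT. Initiation is 90%.

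The screening step separates them (100% against 90%). The initiation step does not.

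**Step 3. Effect on the comparison.** With s and u equal in both arms they cancel, and the home-to-clinic ratio is (1 − t_home)/(1 − t_clinic).

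| t_home | t_clinic | Ratio |
|---|---|---|
| 5% | 2% | 0.95/0.98 = 0.97 |
| 10% | 2% | 0.90/0.98 = 0.92 |
| 10% | 5% | 0.90/0.95 = 0.95 |
| 4% | 10% | 0.96/0.90 = 1.07 |
| 10% | 0% | 0.90/1.00 = 0.90 |
| 0% | 10% | 1.00/0.90 = 1.11 |

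The last two rows are the extremes of the assumed range. With estimated contacts as the denominator, the share identified enters as one more multiplier and the factor is unchanged.

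**Step 4. Against the hypothesised effect.** The sample size section expects 30% initiation under standard care and a doubling. Applied to this proportion, a true change from 30% to 60% would read as 0.60 × 0.95/(0.30 × 0.98) = 1.94-fold at yields of 5% (home) and 2% (clinic), and 0.60 × 0.90/(0.30 × 0.98) = 1.84-fold at 10% and 2%.

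**Step 5. With the combined step.** (TPT or TB treatment)/identified = s × [(1 − t)u + t].
- t = 2%: 0.9 × (0.882 + 0.02) = 0.8118
- t = 5%: 0.9 × (0.855 + 0.05) = 0.8145
- t = 10%: 0.9 × (0.810 + 0.10) = 0.8190

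The ratio at 5% against 2% is 0.8145/0.8118 = 1.003 (as written, 0.97). At 10% against 2% it is 0.8190/0.8118 = 1.009 (as written, 0.92). The small remainder arises because all children with TB are assumed to start treatment, while 90% of TB-free children start TPT.

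**Step 6. When screening differs too.** Assume, per 100 identified, that the clinic arm screens 40 and finds 4 with TB, the home arm screens 90 and finds 4, and all TB-free children start TPT. TPT only gives 36% against 86%: ratio 2.39, difference 50 points. The combined step gives 40% against 90%: ratio 2.25, difference 50 points. The ratio moves by the factor (86/90)/(36/40) = 1.06. The difference does not move, because each arm found the same number of TB cases per 100 identified.

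**The case against.** The strongest reply is that the outcome is correctly named. It is a TB prevention cascade with a step for starting TPT, and a child on TB treatment has not started TPT. The article never calls non-initiation a failure. On that view, TPT alone or a combined step is a choice of estimand. This stands as a reason to keep the TPT-only steps. It does not remove the ambiguity of a compared step in which treated TB and loss from care look alike.

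Other points on that side also stand. Screening is its own compared step, and the child with TB counts as a success there. A reader might infer that the cascade as a whole scores correct care the same as a missed child; the listed steps do not support that. Completion among children who started TPT is already a Table 1 outcome. The factor in Step 3 describes a ratio, and Step 6 shows that a difference in percentage points, which an untransformed t-test compares, may not move at all.

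It can also be said that an analysis plan, which is not shown, may tabulate TB treatment starts. It may. But the article itself fixes the numerator, the denominators and the comparison, and gives a child with TB no end state in either place where it does so.

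**Conclusion.** The point holds for the initiation and completion steps of the secondary continuum-of-care outcome, under either stated denominator. For assumed yields of 0% to 10%, the distortion of the initiation ratio is at most about 10% relative. It rests on a difference in yield between arms that the article neither gives nor rules out.

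Two stronger readings are not supported. A reader might infer that the arm finding more TB must look worse. That follows only with screening and uptake equal; an arm that screens many more children can find more TB and still show higher initiation, and the yield difference could go either way. A reader might also infer that the trial's main result is at risk. The primary endpoint is TPT initiations per index patient and is reported as named, and a distortion of this size is small beside the hypothesised doubling. This is an inexpensive improvement to a secondary comparison.

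**What to change.** Keep the TPT-only cascade steps and the primary endpoint as named. Add to the analysis section that:

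1. TB treatment started is reported as its own end state by arm, using the treatment start date already listed under Outcome data.
2. The proportion started on TPT or TB treatment is compared between arms beside the TPT-only initiation step, over the same identified or estimated denominator.
3. Completion is read among children started on TPT, as Table 1 already does.

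The combined step is preferable to dropping diagnosed children from the denominator. Dropping them conditions on a diagnosis that may itself depend on arm, and it is awkward when the denominator is an estimate from DHS data. The cost is a sentence or two in the plan and one added cascade row that is not nested with the completion step. No new data are needed.

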### Sample size considerations

We considered sample size estimation for the South Africa and Ethiopia sites separately because of the differences in TB epidemiology in the two countries. Sample size calculations were based on the primary outcome which is the clinic-level number of child contacts under age 15 years (Ethiopia) or under 5 years (South Africa) initiating TPT per index patient, compared between the two study arms. We expect there to be a harmonic mean of 51 and 32 diagnosed TB patients per clinic during the study period, in South Africa and Ethiopia respectively. We also expect 20% refusals, withdrawals, or loss to follow-up leading to an average of 40 and 26 TB patients, as reported by the respective TB programs. An estimate of the coefficient of variation (CV) was obtained from a previous contact tracing study in South Africa which was 0.35 [6]. We assumed a similar amount of between-cluster variability in Ethiopia, and we also evaluated how the required sample size changed if we considered a slightly higher CV of 0.4. Prior household-based contact tracing studies and 2016 DHS data showed that households of index TB patients in South Africa and Ethiopia, respectively, have 1.8 and 2.1 children under the age of 15, and we expect that 30% would initiate TPT under the standard of care [6, 29–32]. We hypothesize that the intervention would double the number of children per TB patient initiated on TPT — from 0.5 (=1.8×0.3) to 1 in South Africa, and 0.6 (=2.1×0.3) to 1.2 in Ethiopia. A total of 18 (9 per arm) clinics in each country would be required to detect this effect with 80% power at a 5% level of significance assuming a CV of 0.35. A larger CV of 0.4 would require 20 and 22 clinics in South Africa and Ethiopia, respectively.

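### Poisson regression is named for the count outcomes with no stated allowance for between-clinic variation; with model-based standard errors, the contact-identification test would exceed its 5% level several-fold

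*Protocol article*

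**What the plan says.** Under *Primary and secondary outcome analyses*, the primary outcome has a method suited to the design: "Cluster-level ratios will be compared between arms using an unpaired t-test which has been shown to be robust for a relatively small number of clusters". For the secondary outcomes the section begins with "Secondary outcomes to be compared between arms will be the number of child contacts identified" per index patient. It then states: "As done for the primary outcome, cluster-level summaries for secondary outcomes will also be compared between arms". The next sentence divides the outcomes by type. Proportions go to a t-test, while for counts it says: "Count outcomes will be compared using Poisson regression". It names no standard error, dispersion term, clinic effect or reference distribution for that model.

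Under *Objectives and endpoints* the primary endpoint is "the cluster-level ratio of the number of household child contacts less than 15 years of age in Ethiopia" (under 5 in South Africa) starting TPT per index patient. Table 1 defines contact identification in the same cluster-level form, with the same age limits.

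Under *Sample size considerations* the trial expects clinics to differ: "An estimate of the coefficient of variation (CV) was obtained from a previous contact tracing study in South Africa which was 0.35". For the other country: "We assumed a similar amount of between-cluster variability in Ethiopia". These figures are given for TPT initiation. No CV and no expected rate is given for identification.

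**The concern.** Two outcomes of the same form, from the same 18 clinics per country, are sent to different tests. One allows for variation between clinics. The other, as named, does not. A Poisson model with study arm as the only covariate treats each identified child as an independent event, so differences between clinics that have nothing to do with the intervention enter the arm comparison but not its standard error.

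Identification is more than a descriptive step. The abstract says the trial will determine whether home-based management both identifies more child contacts and starts more of them on TPT. An interval that is too narrow could turn chance differences between clinics into apparent evidence for the first half of that conclusion.

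**Working it through.** **The plan's own figures.** The article states no error rate for the Poisson analysis, so there is none to reproduce. The sample size section serves only as a source of inputs. Its 9 clinics per arm is more than the usual unmatched-cluster formula needs at CV 0.35: 1 + 7.849 × [(0.5+1)/40 + 0.35²(0.5²+1²)]/0.5² = 6.98 in South Africa and, likewise with 0.6, 1.2 and 26, 7.32 in Ethiopia. That gap does not bear on this point.

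**Inputs from the documents.** Clinics per arm per country: 9. Index patients per clinic after losses: "leading to an average of 40 and 26 TB patients" (South Africa, Ethiopia). CV: 0.35, stated for TPT initiation. Ethiopian rates: 0.6 is the expected control-arm TPT initiation per index patient, and so a floor for identification. 2.1 is all children under 15 in the household, and so a ceiling.

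**Assumed inputs.** The same CV for identification, with 0.20 as a lower alternative. 0.3–0.6 under-5 contacts per index patient in South Africa, because the article gives only an under-15 figure (1.8) there. Equal clinic sizes.

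**Step 1: does aggregating to clinics help?** With arm as the only covariate and log(index patients) as offset, the model-based standard error of the log rate ratio is √(1/T₁ + 1/T₀), where T₁ and T₀ are the arm totals. It depends on the totals alone, so it is the same from 18 clinic rows as from individual records. Cluster-level data do not cure the variance assumption.

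**Step 2: understated variance.** If clinic rates vary with CV k, a clinic count with mean μ = rate × m has variance μ(1 + k²μ), not μ. The factor is V = 1 + k²μ. It does not depend on the number of clinics, so adding clinics or pooling countries does not reduce it.

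**Step 3: actual type I error.** α = 2[1 − Φ(1.96/√V)].

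| Country, rate | μ | V at CV 0.35 | α | V at CV 0.20 | α |
|---|---|---|---|---|---|
| Ethiopia, 0.6 | 15.6 | 2.91 | 25% | 1.62 | 12% |
| Ethiopia, 1.2 | 31.2 | 4.82 | 37% | 2.25 | 19% |
| Ethiopia, 2.1 | 54.6 | 7.69 | 48% | 3.18 | 27% |
| South Africa, 0.3 (assumed) | 12 | 2.47 | 21% | 1.48 | 11% |
| South Africa, 0.6 (assumed) | 24 | 3.94 | 32% | 1.96 | 16% |

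Example, Ethiopia at 0.6: T = 9 × 26 × 0.6 = 140.4 per arm. The model-based standard error is √(2/140.4) = 0.119. The true one is 0.119 × √2.91 = 0.204.

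**Step 4: check by simulation.** With 40,000 simulated trials per scenario and gamma-distributed clinic rates, the Ethiopian errors at CV 0.35 were 25.1%, 37.6% and 48.2%, and at CV 0.20 they were 12.2%, 18.9% and 27.2%. Log-normal clinic rates, tried at 2.1, gave 48.1%.

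**Step 5: alternatives.** Across the scenarios simulated at CV 0.35, the cluster-level t-test rejected 4.8–5.0% of the time and quasi-Poisson with t on 16 df 4.8–5.1%. Poisson with a robust sandwich error and a normal reference rejected about 8%.

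**The case against.** The strongest reply is that the article does not say clinic variation will be ignored. It is silent on the variance estimator, the preceding sentence commits to cluster-level comparison, and Table 1 defines the outcome at cluster level. The full protocol and any SAP are not shown, and a robust or overdispersed Poisson model would fit the wording, bringing the error to about 8% or 5%. This part stands: the inflation is conditional on model-based standard errors, and a reader should not infer that the trial will certainly reject a true null 30–50% of the time. It does not remove the point. The sentence names a method for counts and separates it from the t-test given to proportions. Followed as written, it gives intervals that are too narrow, and Step 1 shows that the cluster-level sentence does not change that.

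The second reply concerns the inputs, and most of it stands. The CV belongs to TPT initiation. The Ethiopian rate of 2.1 means complete identification in both arms, where a CV of 0.35 would have to come mostly from differences in household size, so 48% is an outer bound. A reader might also put South Africa's 1.8 children with 40 index patients into the formula and get V = 9.8 and 53%. The documents do not support that figure: 1.8 counts children under 15, and the South African outcome is limited to under 5.

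Third, this concerns secondary analyses only. That is correct and sets the severity.

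**Conclusion.** The point holds in conditional form. As worded, the plan names for its count outcomes a method with no stated allowance for the clinic as the unit of randomisation, and it sits badly with the sentence before it. With model-based standard errors, type I error in Ethiopia would be about 25–48% at CV 0.35 and 12–27% at CV 0.20, over the range from 0.6 to 2.1 contacts identified per index patient. In South Africa it would be about 21–32% at CV 0.35, on an assumed under-5 rate. Every scenario calculated is above twice the nominal 5%. Confidence in the mechanism is high. Confidence in the size is limited by the borrowed CV and the unstated identification rates.

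The primary outcome's t-test and the cluster-level tests of proportions are not affected, and neither the sample size nor trial conduct depends on this sentence. It should be fixed, but it does not threaten the trial's main result.

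**What to change.** Replace the Poisson sentence with: *Count outcomes will be analysed as clinic-level rates per index patient with the same cluster-level t-test as the primary outcome (16 df per country).* The degrees of freedom are 18 clinics minus 2 arms.

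If a count model is preferred, specify quasi-Poisson on the clinic totals with offset log(index patients) and t inference on 16 df. A robust sandwich error with a normal reference is not enough with 18 clusters. If the full protocol or SAP already contains such a correction, state it alongside this sentence.

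The cost is wider intervals for count outcomes. In Ethiopia at CV 0.35 standard errors grow by √2.91 = 1.7 to √7.69 = 2.8 times, and at CV 0.20 by √1.62 = 1.3 to √3.18 = 1.8 times. The t reference adds slightly more. No change to data collection, sample size or the primary analysis is needed.
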